#### Development of Markov model

A health state transition Markov model will be developed using Tree Age pro software (TreeAge Software Inc., Williamstown, Massachusetts, USA) to analyse the cost effectiveness of the intervention. The model will be populated with the caries experience of the children in NPA using the intervention caries data and compared with modelled data from baseline in a non-intervention scenario. The model cohort will start at the age of 6 years where mixed dentition is emerging. The model will track these children up to 17 years using the data from the study for each year. Health states for the model will include “healthy” and “caries” health states. It is anticipated to have health states for conditions such as pulpal abscess as well. The model will be made sensitive for waiting periods, available treatment facilities, availability and costs of resident or fly-in/fly-out professional staff and common practices of the local dental clinics.

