### Aims and hypotheses

The study seeks to (1) assess the effectiveness of an annual oral health preventive intervention in slowing the incidence of dental caries in children in a remote, rural Indigenous setting, (2) identify the mediating role of known risk factors for dental caries and (3) assess the cost-effectiveness and cost-benefit of the intervention.

We hypothesise that 1 and 2 years after the intervention (1) the actual incidence of dental caries in children will be significantly lower than the expected incidence, based on modelling from the two oral health surveys conducted over the past 11 years in the same community, the current survey and (2) the intervention will be cost-effective and cost beneficial, and therefore feasible and sustainable for broader implementation across similar communities in Australia and internationally.

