### Primary outcome variable

The International Caries Detection and Assessment system (ICDAS-II) for clinical caries diagnosis will be used to record caries experience and to determine incidence [36]. This will be measured annually across the 3 years of the study, at baseline and after years 2 and 3 of the project.

ICDAS-II consolidates features of several caries classification systems into one universal system using a six-point ordinal scale ranging from non-cavitated to extensive cavitated lesions to describe any signs of past or present caries activity. Unlike World Health Organisation (WHO) caries detection criteria, ICDAS-II allows the detection of initial/non-cavitated carious lesions, and is thus considerably more sensitive, whilst allowing the extraction of data comparable to previous surveys which used WHO criteria [37].

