### Analysis

All baseline socio-demographic characteristics will be described for the selected sample using counts and frequencies. Baseline and follow-up caries experience and questionnaire related information will be reported. Dental caries increment (incidence) will be the main outcome measure used to determine the effectiveness of the preventive intervention. The expected caries increment will be modelled from the three oral health surveys conducted in this community (2004; 2012 and 2015) and compared with the actual caries increment from 2015–2016; 2016–2017 and 2015–2017. The mean caries increment will be compared between the expected (modelled) and actual findings, and adjusted for known risk factors for dental caries. The hypothesis will be that caries increment observed in the period of 2015 to 2017 is smaller than the modelled caries increments. Two independent samples *t*-test will be used for the analysis with significance being determined if *p* < 0.05.

Children who receive only a part of the intervention will be separately assessed: for example we will have children who fully participate, those with baseline and only a year 1 follow-up, those with baseline and only a year 2 follow-up. This will ‘naturally’ further inform us on the most appropriate frequency of this preventive strategy. Both a group and matched analysis will be conducted to account for children who receive only part of the intervention.

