#### Transition probabilities

Caries increment prior to intervention and post intervention will be used to calculate transition probabilities respectively for the two scenarios of non-intervention and intervention examined by the Markov model. The caries increment rates for intervention will be directly observed. These rates for the non-intervention will be estimated from the modelled data.

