#### Cost utility analysis

The cost utility of the “Big Bang” prevention strategy will be estimated using the Markov model. This analysis will adhere to the best modelling practices as given by International Society for Pharmacoeconomics and Outcomes Research (ISPOR) guidelines [41]. All costs will be presented in 2015 AUD. Costs and outcomes will be discounted at 5 % per year. The model will present the societal perspective. Incremental cost effectiveness ratio (ICER) will be generated by calculating incremental costs for caries treatment divided by the outcome (number of carious lesions prevented and QALYs gained separately). The intervention group will be compared with the modelled values for a non-intervention scenario. To address the uncertainty in the costs and effectiveness estimates, univariate sensitivity analyses will be used. For all probabilities, the 95 % confidence intervals will be used, and for costs high and low values will be estimated. A probabilistic sensitivity analysis will also be performed by re-sampling 1000 times at random from the probability distributions for each parameter. This procedure is similar to multivariate sensitivity analysis and will address the uncertainty of all estimates simultaneously. Gamma distributions will be used for cost estimates and beta distributions will be used for probabilities.

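### The age 6 to 17 Markov model applies rates seen only in the first two years of exposure to all its cycles, and no stated sensitivity analysis varies that assumption

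*Protocol article*

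**What the plan says.** Under Development of Markov model, the article sets the start of the horizon: "The model cohort will start at the age of 6 years where mixed dentition is emerging". It sets the end and the data source in the next sentence: "The model will track these children up to 17 years using the data from the study for each year".

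Under Transition probabilities, the two arms of the model are sourced differently. For the intervention: "The caries increment rates for intervention will be directly observed". For the comparator: "These rates for the non-intervention will be estimated from the modelled data".

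The observation period is short. Primary outcome variable gives the examination schedule: "This will be measured annually across the 3 years of the study, at baseline and after years 2 and 3 of the project". Analysis says the expected increment will be "compared with the actual caries increment from 2015–2016; 2016–2017 and 2015–2017". The effectiveness hypothesis under Aims and hypotheses has the same reach: "We hypothesise that 1 and 2 years after the intervention". Study design has the regime repeated in years 2 and 3, and no examination is planned after the year 3 repeat.

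Cost utility analysis describes the univariate sensitivity work: "For all probabilities, the 95 % confidence intervals will be used, and for costs high and low values will be estimated". It adds a 1000-draw probabilistic analysis, which it says deals with the uncertainty in every estimate at once. Development of Markov model adds service factors: waiting periods, treatment facilities, staffing and its costs, and local clinic practice.

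**The concern.** A rate can be observed at a given age without being observed at a given length of exposure. A modelled 15-year-old who entered at 6 is nine years into the strategy. A 15-year-old in the study is at most two years from the first application, and reached baseline without the earlier years of intervention. Using the second child's rate for the first is an extrapolation, and the article does not call it one.

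The article's own background shows that duration is an open question. It reports that local fluoride levels and mutans streptococci counts return to baseline within months, and that sealing reduces new lesions for up to 48 months. Neither settles what happens over eleven years.

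The second hypothesis, that the intervention is cost-effective and suitable for wider implementation, depends on this model. If the uncertainty analysis varies only sampling error, costs and service factors, the reported interval leaves out an assumption that covers most of the horizon.

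**Working it through.** The article gives no figure of its own to reproduce here. The check counts cycles and weights them.

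**Inputs from the article**
- Model start at age 6, end at 17 (Development of Markov model).
- Two annual intervals per child at most (Primary outcome variable; Analysis).
- Enrolled ages 4–17 (Study participants).
- Discount rate 5% per year (Cost utility analysis).

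**Assumptions**
- Annual cycles, inferred from the reference to study data for each year.
- Equal yearly benefit for the weighting.

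**Age coverage.** Children aged 4–17 at baseline include every modelled age from 6 upwards. There is no gap in age.

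**Cycles beyond observed exposure**
- Model stops on reaching 17: 17 − 6 = 11 cycles; 11 − 2 = 9 unobserved; 9/11 = 82%.
- Age 17 is a full cycle: 12 cycles; 12 − 2 = 10 unobserved; 10/12 = 83%.

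**Discounted weight** (cycle t has weight 1.05^−t, starting at t = 0)
- First two cycles: 1 + 1/1.05 = 1.95.
- 11 cycles: total 8.72; share beyond year 2 = 1 − 1.95/8.72 = 78%.
- 12 cycles: total 9.31; share beyond year 2 = 1 − 1.95/9.31 = 79%.

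**How far the assumption can move total benefit** (11 cycles, in units of one undiscounted year's effect; weight after year 2 is 8.72 − 1.95 = 6.77). The later effects below are illustrations, not figures from the article.

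| Effect after year 2 | Discounted benefit | Relative to maintained |
|---|---|---|
| Half as large again | 1.95 + 1.5 × 6.77 = 12.11 | 1.39 |
| Maintained | 8.72 | 1.00 |
| Halved | 1.95 + 0.5 × 6.77 = 5.34 | 0.61 |
| Nil | 1.95 | 0.22 |

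If yearly intervention costs continue unchanged, intervention cost per unit of benefit relative to the maintained case is 8.72/12.11 = 0.72, 8.72/5.34 = 1.6 and 8.72/1.95 = 4.5 for the other three rows. This is not the article's ICER, which also involves caries treatment costs.

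**What the stated sensitivity analyses reach.** Confidence limits and resampling describe how precisely the first- and second-year rates are estimated. They cannot show whether those rates hold in years 3 to 11. High and low costs and the service factors do not bear on it either.

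**The case against.** The strongest reply is that an age-based synthetic cohort is a normal way to build such a model, and is the natural reading of the horizon sentence. The statement that rates are directly observed is there to contrast them with the modelled comparator; it does not claim eleven years of follow-up. This stands as far as it goes. A reader might infer that the model lacks data for some ages, or that the article makes a false claim of long follow-up. The text supports neither. The gap is in length of exposure only.

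A second reply is that this is a condensed article. Scenario lists often sit in a fuller economic plan, and the article commits to ISPOR modelling guidance. A persistence parameter is therefore not excluded. But the article does set out its sensitivity set and says that resampling covers all estimates at once. On the text shown, that statement is too broad.

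Third, the study collects relevant data: sealant retention at follow-up, and a separate assessment of partly treated children. Both are useful, but both stay within the two-year window.

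Fourth, a reader might infer that the model will flatter the intervention. The documents do not support a direction. The article regards sealing newly erupted teeth as the best way to prevent fissure caries, so children treated from age 6 could do better than older study children who started late. A nil effect under continued annual application would be extreme. Two further inferences also lack support: the article does not state that modelled children are treated every year to 17, nor that later rounds mainly reach newly erupted teeth.

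**Conclusion.** The point holds as one of unlabelled and untested extrapolation over length of exposure. With annual cycles, 9 of 11 (or 10 of 12) lie beyond the two years for which any child is observed. They carry 78–79% of discounted weight if yearly benefit is equal. The direction of any error is unknown, and the multiples in the table are illustrations of sensitivity, not estimates of bias or of the ICER.

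It would go too far to conclude that the age 6 to 17 horizon is wrong or that it should be replaced. A long horizon is needed to capture later treatment costs. The defect is that the assumption about the later effect is not stated and that the described uncertainty analysis cannot reflect it. This limits what the model can say on the second hypothesis and is worth correcting.

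**What to change.** 1. **Transition probabilities:** say that intervention rates are observed for the first two years of exposure.
2. **Development of Markov model:** state whether the model repeats the intervention every year and what effect is assumed after year 2, and label those cycles as extrapolation.
3. **Cost utility analysis:** add scenario analyses on the effect after year 2, for example stronger, maintained, halved and nil, informed by the sealant retention already planned under Secondary outcome variables. Limit the statement about resampling to uncertainty in the estimated parameters.
4. **Reporting:** give a two-year within-study result as a secondary analysis beside the age 6 to 17 result.

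The cost is a few more model runs, some wording, and a wider cost-effectiveness statement. No extra data collection is needed.

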#### Costs calculations

The costs of providing the preventive intervention, the costs of all treatment for carious lesions, and the out-of-pocket costs in relation to caries experience will be assessed. These costs will be assigned to each child taking into account the number of surfaces treated. Cost intervention will include sealants, an oral anti-septic application, application of a fluoride varnish and including cost for human resources and logistics. The costs of treating incremental caries will be estimated using government costs for treatments. Total out-of-pocket costs for parents of children with caries will be calculated based on the quantities of resource use provided in the surveys. Mean, median and interquartile range costs will be presented for each major treatment category in caries. All costs will be presented in 2015 AUD.

#### Estimation of utility weights

The utility values for dental health states will be estimated from the CHU-9D data. Using the CHU-9D (Child Health Utility) multi attribute utility instrument, quality of life scores (utility scores) for each caries severity level experienced by the children will be determined. A scoring algorithm that has been validated in the UK for CHU-9D for children will be applied [38]. Utility scores will be presented for different age groups and gender. These values will contribute to estimate Quality Adjusted Life Years (QALYs). The CHU-9D will be validated in a similar Indigenous population prior to the application in the study population.

#### Transition probabilities

Caries increment prior to intervention and post intervention will be used to calculate transition probabilities respectively for the two scenarios of non-intervention and intervention examined by the Markov model. The caries increment rates for intervention will be directly observed. These rates for the non-intervention will be estimated from the modelled data.

#### Cost utility analysis

The cost utility of the “Big Bang” prevention strategy will be estimated using the Markov model. This analysis will adhere to the best modelling practices as given by International Society for Pharmacoeconomics and Outcomes Research (ISPOR) guidelines [41]. All costs will be presented in 2015 AUD. Costs and outcomes will be discounted at 5 % per year. The model will present the societal perspective. Incremental cost effectiveness ratio (ICER) will be generated by calculating incremental costs for caries treatment divided by the outcome (number of carious lesions prevented and QALYs gained separately). The intervention group will be compared with the modelled values for a non-intervention scenario. To address the uncertainty in the costs and effectiveness estimates, univariate sensitivity analyses will be used. For all probabilities, the 95 % confidence intervals will be used, and for costs high and low values will be estimated. A probabilistic sensitivity analysis will also be performed by re-sampling 1000 times at random from the probability distributions for each parameter. This procedure is similar to multivariate sensitivity analysis and will address the uncertainty of all estimates simultaneously. Gamma distributions will be used for cost estimates and beta distributions will be used for probabilities.

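### The stated ICER numerator counts caries-treatment cost only, which conflicts with the societal perspective and with the intervention and out-of-pocket costs the protocol plans to collect

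*Protocol article*

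**What the plan says.** Under Cost utility analysis the article defines the ratio: "Incremental cost effectiveness ratio (ICER) will be generated by calculating incremental costs for caries treatment divided by the outcome". There are two denominators, "number of carious lesions prevented and QALYs gained separately". The comparator is modelled: "The intervention group will be compared with the modelled values for a non-intervention scenario". The same section states: "The model will present the societal perspective".

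Other sections describe a wider set of costs:

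- Costs calculations opens with "The costs of providing the preventive intervention, the costs of all treatment for carious lesions" and adds families' out-of-pocket costs as a third item. It continues: "These costs will be assigned to each child taking into account the number of surfaces treated". Intervention cost there covers materials, staff and logistics.
- Secondary outcome variables plans to record programme costs, participants' costs of attending, and emergency treatment between annual visits.
- The Discussion expects programme cost to be set against the cost of letting new lesions develop.

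The second hypothesis, under Aims and hypotheses, is that "the intervention will be cost-effective and cost beneficial, and therefore feasible and sustainable for broader implementation".

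**The concern.** An ICER is the difference in total cost between two strategies divided by the difference in outcome. The stated numerator contains one of the three cost categories that Costs calculations lists. Because that section separates treatment of lesions from the preventive intervention, the phrase in the formula cannot easily be read as covering both.

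Aim 3 and the second hypothesis are at stake. The question is whether one annual visit to a remote, resource-constrained community is worth its cost. A ratio without the cost of that visit cannot answer it. The planned sensitivity analyses would not reveal the problem either: varying a cost that is not in the ratio cannot move the ratio.

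**Working it through.** The article states no ICER, unit cost or effect size, so there is no figure to reproduce. The check is algebra, followed by an illustration on assumed inputs.

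**Notation, per child.** I = intervention cost; T1 and T0 = caries-treatment cost with and without the intervention; O1 and O0 = out-of-pocket and emergency cost with and without it; E = outcome gained (lesions prevented or QALYs).

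- Formula as written: (T1 - T0)/E
- Total societal cost: [(I + T1 + O1) - (T0 + O0)]/E
- Omitted: (I + O1 - O0)/E

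I does not appear in the first line. That follows from the wording, for both denominators, and needs no assumed number.

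**Per lesion prevented, same share of lesions treated in both scenarios.** Let L be lesions prevented and T the treatment cost per lesion, so T1 - T0 = -T x L. Set O1 = O0 for simplicity.

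- As written: (-T x L)/L = -T
- Total cost: (I - T x L)/L = I/L - T

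Example with assumed L = 0.5, T = AUD 200, I = AUD 150: as written, -100/0.5 = AUD -200; total cost, (150 - 100)/0.5 = AUD +100.

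Total-cost ICER (AUD per lesion prevented) over the assumed ranges:

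| T | I | L = 0.25 | L = 0.5 | L = 1.0 | As written |
|---|---|---|---|---|---|
| 100 | 50 | 100 | 0 | -50 | -100 |
| 100 | 150 | 500 | 200 | 50 | -100 |
| 100 | 300 | 1,100 | 500 | 200 | -100 |
| 200 | 50 | 0 | -100 | -150 | -200 |
| 200 | 150 | 400 | 100 | -50 | -200 |
| 200 | 300 | 1,000 | 400 | 100 | -200 |

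The literal result does not respond to I or L. The total-cost result runs from -150 to +1,100 and changes sign.

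**Different treatment provision.** Study design has all active disease treated before the preventive intervention, whereas the Background reports few restored teeth in the 2004 and 2012 surveys. Assume T = AUD 200, 2.0 lesions without and 1.5 with the intervention, all treated under the intervention, and a share p treated without it. The literal numerator is 200 x (1.5 - 2.0p):

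- p = 100%: -100
- p = 75%: 0
- p = 60%: +60
- p = 30%: +180

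Counting b lesions per child of baseline backlog in the intervention scenario only, with p = 100%, gives 200 x (b + 1.5 - 2.0). This is 0 at b = 0.5 and +100 at b = 1. The sign of the literal numerator therefore depends on how restorative work is counted.

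**The case against.** The strongest reply is that this is one loose sentence in a condensed article. Nothing says programme cost is excluded. It is to be recorded, assigned to each child and compared with the cost of new lesions. Development of Markov model makes the model sensitive to the cost of resident or fly-in staff, and the analysis is to follow ISPOR guidance. This stands as evidence of intent: programme cost was very probably meant to count. It does not rescue the sentence, which is the only formula given and is wrong as stated. A wrong rule is different from detail left to a fuller plan.

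A reader might also infer that any effective programme must appear cost-saving, so that the economic hypothesis could not fail. The documents do not support that. It needs literal application of the formula and equal treatment provision in both scenarios, and the article points away from equal provision. The -T result also belongs to the per-lesion ratio only. The cost-per-QALY ratio omits I as well, but does not reduce to a constant.

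Finally, the primary caries comparison is untouched. That is correct and limits the point to the economic aim.

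**Conclusion.** The point holds as an internal contradiction in the economic plan. As written, the ICER omits intervention and family costs, contrary to the declared perspective and the planned cost collection, and so cannot answer aim 3. That the result is independent of programme cost rests on the wording alone. The size is illustrative: under equal treatment provision, no difference in out-of-pocket or emergency cost, and the assumed unit costs and effects, the per-lesion figure is AUD -100 to -200 as written against AUD -150 to +1,100 on total cost. With unequal provision the literal numerator can take either sign, so no fixed direction of error can be claimed for it.

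**What to change.** Rewrite the ICER sentence so that the numerator is total societal cost in the intervention scenario minus total societal cost in the modelled non-intervention scenario. Total cost should comprise the intervention (including staff, travel and logistics), caries treatment, emergency care and out-of-pocket costs. Divide by lesions prevented and by QALYs gained, separately. State how restorative treatment, including any baseline backlog, is counted in each scenario, and use the same basis in both.

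This costs one rewritten sentence and a line on allocation; the cost items are already planned for collection. Adding intervention cost makes the ICER less favourable, although averted emergency and family costs may partly offset that. Net monetary benefit from the same inputs would be a useful but optional addition, and would need a stated threshold.
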